## 1. Abstract

Patients with cancer often undergo costly therapy and acute care utilization that is discordant with their wishes, particularly at the end of life. Early serious illness conversations (SIC) improve goal-concordant care, and accurate prognostication is critical to inform the timing and content of these discussions. In this project, we will evaluate a health system initiative that uses a machine learning algorithm to predict patients with a higher risk of short-term mortality and then prompts oncologists to SICs with these patients. In partnership with the health system, this will be conducted as a cluster-randomized trial to evaluate its effect.

## 2. Overall objectives

The objective of the study is to evaluate the effect of a health system initiative using machine learning algorithms and behavioral nudges to prompt oncologists to have serious illness conversations with patients at high-risk of short-term mortality.

## 3. Aims

### *3.1 Primary outcome*

The primary outcome is change in the proportion of patients that have an outpatient oncology visit with documentation of a serious illness conversation (SIC).

### *3.2 Secondary outcome*

The secondary outcomes are: 1) the change in the proportion of patients who have an outpatient oncology visit and are identified as high-risk by the machine learning algorithm with documentation of a SIC; 2) the change in the proportion of patients that have an outpatient oncology visit with documentation of advanced care planning (ACP).

### *3.3 Exploratory outcomes*

- Acute care utilization metrics, including Oncology Evaluation Center, ED, Inpatient and ICU admissions.
- Healthcare utilization in the last 30 days of life in Penn Medicine facilities: acute care utilization as above, plus receipt of chemotherapy in the last 30 days.

## 4. Background

Patients with cancer often undergo costly therapy and acute care utilization that is discordant with their wishes, particularly at the end of life. Early serious illness conversations (SICs) to determine a patient's goals and values for therapy can increase goal-concordant care. Nevertheless most patients with advanced cancer die without a documented SIC, including the vast majority of UPHS oncology patients in 2018. A key reason for this gap may be that oncologists routinely overestimate life expectancy of patients with advanced cancer, delaying SICs until late in the disease course and resulting in aggressive care near the end of life.

Existing prognostic aids in oncology are rarely used because they do not apply to most cancers,, do not identify most patients who will die within 1 year, and require time-consuming data input. Electronic health record (EHR)-based predictive algorithms can improve clinician decision-making in acute care settings, but it is unclear whether such algorithms can guide clinicians to perform SICs. As oncologists strive to assess patients' goals earlier in the disease course, accurate prognostication is critical to inform the timing and content of these discussions.

## 5. Study design

### *5.1 Design*

This study will use a stepped-wedge cluster randomized trial to evaluate a health system initiative. Oncology practices will be randomly assigned in sequential four-week blocks to receive the email prompt intervention, in which individual oncologists will receive an automated weekly email detailing 1) how many serious illness conversations they have had, 2) how their number of serious illness conversations compares to peer oncology providers across UPHS, and 3) a weekly roster of their upcoming patients at high risk of short-term mortality as determined by our mortality prediction algorithm (see below), viewable on a HIPAA-compliant secure web interface. Clinicians will receive a HIPAA compliant text message on the morning of the appointment reminding them to consider a serious illness conversation with patients on the list. Providers may opt out of this reminder on the web interface containing the weekly patient roster of high risk patients. Prior to receiving the intervention, practices will receive current standard communications regarding serious illness performance until they are randomized to the intervention. Practices will be cluster-randomized to the intervention over a 16-week period, after which all practice physicians will receive the email intervention.

### *5.2 Study duration*

The study is expected to begin in June 2019 and take 10 months (16 weeks for intervention + 24 weeks followup) to complete.

### *5.3 Target population*

Medical oncology clinicians (physicians, nurse practitioners and physician assistants) and their patients at the University of Pennsylvania Health System practicing at one of two hematology/oncology practices: The Perelman Center for Advanced Medicine (PCAM) and Pennsylvania Hospital (PAH).

### *5.4 Accrual*

Patients will accrue to the trial as their clinical practice receives the email intervention. Eight University of Pennsylvania oncology practices will be randomly assigned to one of four start dates separated by four weeks, resulting in four pairs of clinics starting the intervention two clinics at a time every four weeks over sixteen weeks. When a clinic reaches the assigned start date for the intervention arm, the clinicians will begin to receive the weekly email intervention and text reminders. Based on previous studies and assuming a baseline SIC rate of 0.65 SICs per

provider per 4-weeks, we believe we will have over 80% power to detect a 60% increase in SIC rates per provider per 4-weeks.

### *5.5 Key inclusion criteria*

Oncologists must meet the following criteria to be eligible for the study:

1) Care for adults with cancer at the following oncology clinics at the University of Pennsylvania Health System:

1. Perelman Center for Advanced Medicine:

- Breast Oncology
- Gastrointestinal Oncology
- Genitourinary Oncology
- Lymphoma
- Melanoma and Central Nervous System Oncology (grouped together due to low number of providers)
- Myeloma
- Thoracic / Head and Neck Oncology (one group, not a combination of subspecialties)

2. Pennsylvania Hospital Oncology

### *5.6 Key exclusion criteria*

- Providers at these clinics who care for only patients with benign hematologic disorders or who only see genetics consults will be excluded and not receive any emails.
- Providers who see less than 12 high-risk patients in either the pre- or post-intervention periods
- Visits for patients with lung cancer who are enrolled in an ongoing palliative care clinical trial that may lead to more SICs.
- Patient visits that are for oncology genetics consults (such patients may still be included if they see their primary oncologist during the trial)
- Providers who have not undergone Serious Illness Conversation Program training

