### 8.2 Procedures

Data on oncologists and their patients at the University of Pennsylvania Health System will be obtained from Penn Data Store and Clarity (Epic's data reporting database). Physician data includes demographic information (e.g. sex, type of medical degree, etc.) and may be also obtained from publicly available databases or websites online. The predictive algorithm identifies high-risk patients based on demographic information, information about comorbid conditions (including type of cancer; other variables like diabetes, hypertension, and chronic kidney disease, and comorbid conditions needed to calculate the Charleston Comorbidity Index; laboratory test results; and previous emergency department and hospital admissions. This predictive algorithm has been validated and results are currently being submitted for publication in a medical journal. Clarity will be used to identify documentation of SICs and ACP.

After identifying eligible oncologists, block randomization will occur at the clinic level (noting that PCAM melanoma and CNS Oncology will be randomized together as both clinics have a low number of providers). We will obtain baseline measures and plan to stratify the randomization by those above and below median level of SICPs in March through May of 2019.

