## 9. Analysis plan

All analyses will be conducted using intention-to-treat using the patient as the unit of analysis and clustering at the level of the oncologist. Advanced practice providers (APPs) will receive the intervention, but will be associated with the oncologist with whom they work for the purposes of the analysis. All hypothesis tests will use a two-sided alpha of 0.05 as our threshold for statistical significance.

The primary and secondary outcome measures will use a binary indicator representing the presences of an SIC or ACP for each patient. The primary outcome will be expressed as a standardized rate of documented SIC discussions (number of documented SIC notes / 100 unique patient visits). In the main adjusted analysis, we will fit models using generalized estimating equations cluster on oncologists, using group (oncology practices) and period (4-week increments) fixed effects and adjusting for monthly temporal trends.

To test the robustness of our findings, we will perform sensitivity analyses that adjusts for available patient characteristics and comorbidities such as demographics and the Charlson Comorbidity Index.

Additional sensitivity analyses will include:

- Including patients enrolled in aforementioned palliative care lung cancer trial
- Analyzing results clustering at the level of the clinician (oncologist or APP)

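### The 12-patient exclusion uses a post-randomisation count, so it conflicts with the stated order of randomisation and with intention-to-treat, and on the natural reading it depends on the randomised start date

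*Protocol*

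**What the plan says.** Section 5.6 lists among the exclusions "Providers who see less than 12 high-risk patients in either the pre- or post-intervention periods". The protocol defines neither period. For providers who see only benign haematology or genetics consults, the same list says that they get no emails. It says nothing of the kind for low-volume providers.

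Three other sections bear on the rule:

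- **Order of events (section 8.2).** "After identifying eligible oncologists, block randomization will occur at the clinic level". Baseline measures are also to be obtained, and randomisation is to be stratified on the SIC level in March to May 2019.
- **What is randomised (section 5.4).** "Eight University of Pennsylvania oncology practices will be randomly assigned to one of four start dates separated by four weeks". Section 5.1 adds: "Practices will be cluster-randomized to the intervention over a 16-week period, after which all practice physicians will receive the email intervention". Section 5.2 has the study "take 10 months (16 weeks for intervention + 24 weeks followup) to complete".
- **Analysis population (section 9).** "All analyses will be conducted using intention-to-treat using the patient as the unit of analysis and clustering at the level of the oncologist". The sensitivity analyses listed there adjust for patient characteristics, add back patients in the lung cancer trial, and cluster on the clinician. None restores providers removed by the volume rule.

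**The concern.** An eligibility rule should be decidable when units are randomised. Half of this one is not, because the post-intervention count does not yet exist. In practice the rule would remove providers from the analysis after their practice has been allocated, and possibly after they have received the emails.

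A stepped wedge adds a second difficulty. The start date is what is randomised, and it fixes how long a practice spends in control and in intervention time. A fixed count of 12 is then easier or harder to reach according to allocation. Providers would be lost unevenly across the four start dates, and the survivors in a short window would be selected for high volume. With eight practices in four pairs, heavy loss in one pair weakens the comparison on which the design rests. Because the periods are undefined, the choice of which pairs lose providers could also be made after the data are seen.

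**Working it through.** **Conflicts that need no arithmetic.** Section 8.2 settles eligibility and then randomises. Section 5.6 makes eligibility depend partly on a count from the post-intervention period. Both cannot be followed. Section 9 analyses by intention-to-treat, while section 5.6 removes randomised providers on later data. Both cannot hold.

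**Is there a figure to reproduce?** The protocol gives no retention figure. Its power statement in section 5.4 (over 80% for a 60% increase from 0.65 SICs per provider per 4 weeks) gives no number of providers and no intracluster correlation. It cannot be reproduced and does not bear on this point.

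**Inputs from the protocol.** Threshold of 12 in each period; four start dates 4 weeks apart; 16 weeks of roll-out plus 24 of follow-up, so 40 weeks; baseline window March to May 2019, which is 92 days, or 92/7 = about 13.1 weeks.

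**Assumed.** Each provider's high-risk patients arrive as a Poisson count at a constant rate r per week. The protocol states no volume. It also does not say whether the first pair starts at week 0 or after a 4-week control block, so both are shown.

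**Formula.** Retention = P(Poisson(r × pre-weeks) ≥ 12) × P(Poisson(r × post-weeks) ≥ 12).

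The main building blocks for P(X ≥ 12) are 11.2% at mean 8, 53.8% at mean 12, 87.3% at mean 16 and 99.7% at mean 24. For example, a start at week 4 of 40 with r = 2 has a pre mean of 8 and a post mean of 72. Retention is 0.112 × 1.000 = 11%.

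| Reading of pre and post | r | 1st | 2nd | 3rd | 4th |
|---|---|---|---|---|---|
| Starts 4, 8, 12, 16 of 40 weeks | 1 | 0.1% | 11% | 54% | 87% |
| same | 2 | 11% | 87% | 99.7% | 100% |
| same | 3 | 54% | 99.7% | 100% | 100% |
| same | 5 | 98% | 100% | 100% | 100% |
| Starts 0, 4, 8, 12 of 40 weeks, in-trial time only | 2 | 0% | 11% | 87% | 99.7% |
| Starts 0, 4, 8, 12, the 16-week roll-out only | 2 | 0% | 11% | 76% | 11% |
| Starts 0, 4, 8, 12; March to May added to pre, follow-up in post | 1 | 66% | 92% | 99% | 99.8% |
| same | 2 | about 100% | 100% | 100% | 100% |

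The last reading at r = 1 uses pre windows of 13.1, 17.1, 21.1 and 25.1 weeks and post windows of 40, 36, 32 and 28 weeks. In the week-0 readings limited to in-trial time, the first pair has no pre-period, so all its providers are excluded whatever their volume.

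**Windows common to everyone.** With an assumed 13-week baseline and 24-week follow-up for all, exclusion is 36% at r = 1, 2.7% at r = 1.5 and 0.1% at r = 2, the same for every start date. The dependence on start date disappears, but the follow-up count is still post-randomisation.

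**The case against.** The strongest reply is that the size is unknown and may be nil. The protocol gives 24 weeks of follow-up and names a March to May baseline. If both count, no pair has a short window and retention is about 100% at 2 per week. Above about 5 per week the loss is small on every reading in which all pairs have a pre-period. The reading that removes the whole first pair is hardly what was intended. All of this stands. The rates are assumptions, and the start-date dependence would vanish under calendar windows common to all practices. The protocol states no such windows, however. An SAP could define them, but a definition alone would not make a post-intervention count available before randomisation, nor reconcile it with intention-to-treat.

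A reader might infer three stronger claims that the document does not support:

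- **Bias as large as the target effect.** In a 4-week window at 2 per week, providers who pass average 13.2 high-risk patients against 8 expected, a ratio of 1.64, which looks like the 60% increase in the power statement. But it is a ratio of patient counts. The primary outcome is SIC notes per 100 unique patient visits, and extra high-risk patients also enter the denominator. The ratio falls to 1.06 at an expected count of 16 and 1.001 at 24. The two figures are not comparable.
- **A known direction of bias.** The filter acts on patient volume, not directly on the outcome. Nothing in the protocol shows how volume relates to the SIC rate.
- **The emails change the count itself.** High-risk status comes from an algorithm on demographics, comorbidities, laboratory results and earlier admissions, applied to clinic schedules. An indirect effect is conceivable, but no mechanism is described, and the point does not need one.

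**Conclusion.** The rule is wrong as written. That the post-intervention count conflicts with the order of events in section 8.2 and with intention-to-treat in section 9 follows from the text alone and rests on no assumption. That the hurdle varies with allocation holds if pre and post are each practice's own control and intervention time, the natural reading in a stepped wedge.

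How many providers are lost, and from which pairs, depends on two things the protocol does not give: the windows and the high-risk volume per provider. Under the Poisson assumption the loss runs from negligible to a whole pair. It is large at about 1 to 3 patients per week when only in-trial time counts. Neither the size nor the direction of any resulting bias in the SIC rate can be determined from the document.

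**What to change.** Replace the criterion in section 5.6 with a volume threshold applied in one pre-randomisation window common to all practices, for example fewer than 12 high-risk patients in March to May 2019. Freeze the provider list at randomisation, and state in section 9 that every listed provider is analysed in all periods whatever the later volume. The 12-patient restriction on post-randomisation data can be kept as a sensitivity analysis, with its periods defined.

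The cost is small. The algorithm must be run on the schedules for that window, since section 8.2 names only SIC levels for March to May and not high-risk counts. Some providers whose volume later proves low will stay in the analysis and contribute little.

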## **6. Subject recruitment**

Information on oncology practices and their clinicians at the University of Pennsylvania Health system will be identified by department leadership. High-risk patients will be identified by applying our mortality prediction algorithm (which uses electronic health record data from Clarity, an EPIC reporting database) to weekly oncology clinic schedules.

## **7. Subject compensation**

No compensation will be offered in this study.

## 8. Study procedures

### 8.1 Consent

A waiver of informed consent is requested. This is a health system initiative that will be implemented. The study is to evaluate that initiative. Therefore, physicians and their patients will not be consented as this is the standard of practice per the health system initiative. Without a waiver of the consent, the initiative would still be implemented by the health system, but the study would be infeasible. There are several additional reasons why we feel a waiver of consent should be granted. First, it is not feasible to consent every physician and as mentioned this initiative would occur with or without the study of it. Second, if members of the control group were consented, this alone could change their behavior. This could potentially disrupt the design of the study and making interpretation of the findings challenging. Third, physicians are not being forced to have serious illness conversations for their patients. Instead, they are being reminded of their patients at high-risk of mortality and receiving an email prompt regarding the number of serious illness conversations that they have had, , with opt-out text message reminders on the day of the appointment. This is no different than standard of care in which a physician would review the same information and decide to have a serious illness conversation. The initiative is simply a reminder for the physician and makes their standard of care process easier to conduct. Finally, as part of a previous quality improvement initiative, we previously interviewed 40 patients after a serious illness conversation with their oncologist. We found no evidence of harm and found that serious illness conversations were considered standard of care for patients with cancer.

### 8.2 Procedures

Data on oncologists and their patients at the University of Pennsylvania Health System will be obtained from Penn Data Store and Clarity (Epic's data reporting database). Physician data includes demographic information (e.g. sex, type of medical degree, etc.) and may be also obtained from publicly available databases or websites online. The predictive algorithm identifies high-risk patients based on demographic information, information about comorbid conditions (including type of cancer; other variables like diabetes, hypertension, and chronic kidney disease, and comorbid conditions needed to calculate the Charleston Comorbidity Index; laboratory test results; and previous emergency department and hospital admissions. This predictive algorithm has been validated and results are currently being submitted for publication in a medical journal. Clarity will be used to identify documentation of SICs and ACP.

After identifying eligible oncologists, block randomization will occur at the clinic level (noting that PCAM melanoma and CNS Oncology will be randomized together as both clinics have a low number of providers). We will obtain baseline measures and plan to stratify the randomization by those above and below median level of SICPs in March through May of 2019.

## 9. Analysis plan

All analyses will be conducted using intention-to-treat using the patient as the unit of analysis and clustering at the level of the oncologist. Advanced practice providers (APPs) will receive the intervention, but will be associated with the oncologist with whom they work for the purposes of the analysis. All hypothesis tests will use a two-sided alpha of 0.05 as our threshold for statistical significance.

The primary and secondary outcome measures will use a binary indicator representing the presences of an SIC or ACP for each patient. The primary outcome will be expressed as a standardized rate of documented SIC discussions (number of documented SIC notes / 100 unique patient visits). In the main adjusted analysis, we will fit models using generalized estimating equations cluster on oncologists, using group (oncology practices) and period (4-week increments) fixed effects and adjusting for monthly temporal trends.

To test the robustness of our findings, we will perform sensitivity analyses that adjusts for available patient characteristics and comorbidities such as demographics and the Charlson Comorbidity Index.

Additional sensitivity analyses will include:

- Including patients enrolled in aforementioned palliative care lung cancer trial
- Analyzing results clustering at the level of the clinician (oncologist or APP)

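### Eight practices are randomised but the primary model clusters on oncologists, so its standard error can be too small if practices shift over time

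*Protocol*

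**What the plan says.** Protocol section 8.2 states that "block randomization will occur at the clinic level". Section 5.4 gives the numbers: "Eight University of Pennsylvania oncology practices will be randomly assigned to one of four start dates separated by four weeks", two practices per date. Section 8.2 adds an intention to stratify by whether baseline conversation levels lie above or below the median.

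Section 9 sets the analysis "using the patient as the unit of analysis and clustering at the level of the oncologist". The main model is "generalized estimating equations cluster on oncologists, using group (oncology practices) and period (4-week increments) fixed effects and adjusting for monthly temporal trends". Section 9 also says "All hypothesis tests will use a two-sided alpha of 0.05" as the threshold.

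The only other clustering level named is a sensitivity analysis at the level of the individual clinician, oncologist or advanced practice provider (APP). The protocol mentions no practice-level variance, practice-by-period term, small-sample correction or randomisation-based test. A statistical analysis plan may exist, but this is not a detail left to it: the protocol itself fixes the clustering level, below the unit of assignment.

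**The concern.** The intervention switches on for a whole practice on one date, so the treatment indicator varies only by practice and period. Anything that moves documentation for a whole practice in one period is then confounded with treatment in that cell. It is also shared by every oncologist in the practice. A variance clustered on oncologists treats those colleagues as independent replicates and leaves the shared part out.

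The planned clinician-level analysis is finer still, so it cannot show whether this matters. At stake are the primary p-value and confidence interval. Where the error occurs, it favours a positive finding.

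**Working it through.** **Inputs from the protocol.** Eight practices, four start dates, two practices per date (5.4); four-week periods and a 16-week roll-out (5.1); 0.65 conversations per provider per four weeks (5.4); practice and period main effects, clustering on oncologist, two-sided 0.05 (9).

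**Not in the protocol, so assumed.** Oncologists per practice (m), the practice-by-period SD on the log scale (s), and the number of blocks before the first start date.

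**The plan's own figure.** Section 5.4 claims over 80% power for a 60% increase. It gives no number of providers, so the claim can be neither reproduced nor refuted and is not part of this point.

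**Step 1: what the variance leaves out.** Write the log rate in practice i, period t as practice effect + period effect + treatment effect + c(i,t), with c(i,t) having SD s. Treating counts as Poisson, the log of the practice-period rate has variance of about 1/(0.65m) + s². Oncologist clustering captures the first term only. So, approximately:

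reported SE / true SD = √[ (1/(0.65m)) / (1/(0.65m) + s²) ]

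true rejection rate = 2 × [1 − Φ(1.96 × ratio)]

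| m | 1/(0.65m) | s | ratio | rejection |
|---|---|---|---|---|
| 3 | 0.513 | 0.2 | 0.963 | 5.9% |
| 3 | 0.513 | 0.3 | 0.922 | 7.1% |
| 5 | 0.308 | 0.2 | 0.941 | 6.5% |
| 5 | 0.308 | 0.3 | 0.880 | 8.5% |
| 10 | 0.154 | 0.1 | 0.969 | 5.8% |
| 10 | 0.154 | 0.2 | 0.891 | 8.1% |
| 10 | 0.154 | 0.3 | 0.794 | 11.9% |

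These large-sample figures isolate the clustering level and leave out small-sample error. The excess grows with s and with m. For scale, a one-SD shift multiplies the rate by e^0.2 = 1.22 or e^0.3 = 1.35.

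**Step 2: simulation with Poisson counts.** No effect, 1,000 trials per setting, m = 5 or 10, and 4, 5 or 7 blocks. Log-scale SD was 0.5 between oncologists and 0.3 between practices. Monte Carlo error is about 0.7 to 1.4 percentage points. Rejection with oncologist clustering, as the range over settings:

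- s = 0: 4.4-8.9%
- s = 0.1: 5.3-7.3%
- s = 0.2: 7.5-10.3%
- s = 0.3: 10.4-14.2%
- s = 0.5: 15.2-24.0%

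With 5 blocks, m = 10 and s = 0.3, the true SD is 0.282 against a mean reported SE of 0.227. The ratio is 0.805, close to the 0.794 of step 1. It implies 2 × [1 − Φ(1.578)] = 11.5%; the simulation gave 10.9%.

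**Step 3: simulation with binary patient outcomes**, closer to section 9. With m from 3 to 10 and 5 or 7 blocks, rejection is about 6-8% at s = 0, 9-11% at s = 0.2 and 10-13% at s = 0.3. The 6-8% at s = 0 is a small-sample excess and has nothing to do with shared practice shifts.

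**Step 4: alternatives.** In the step 2 trials, clustering on the eight practices with a plain z test rejects 12-18%, worse than oncologist clustering in every setting up to s = 0.3. Multiplying the SE by √(8/7) and using t on 7 degrees of freedom gives 6.0-9.2%. A permutation test over stratified start dates rejects about 4-7% with the binary outcomes of step 3, and 4.7-4.9% in a separate count simulation of 3,000 trials per setting.

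**Step 5: is a permutation test usable with eight practices?** Unstratified, there are 8!/(2!)⁴ = 40,320/16 = 2,520 allocations. If each start date takes one practice from each of two strata of four, there are 4! × 4! = 576. The protocol does not state that arrangement, so 576 is an assumption. Either way the smallest attainable p (1/576 = 0.0017 or 1/2,520 = 0.0004) is far below 0.05.

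**The case against.** The best defence is that practice fixed effects already deal with clustering by practice, so oncologists within a practice can count as independent. That holds for differences constant over time, and period effects deal with system-wide change. It fails for shifts specific to one practice in one period.

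The second defence is about size, and much of it stands. The protocol gives no practice-by-period variance. At SD 0.1 the simulated rates cannot be told apart from those at zero. With an assumed between-practice SD of 0.3, a practice-by-period SD of 0.3 means that four-weekly shocks are as large as all stable practice differences: 0.09/(0.09 + 0.09) = 0.50 of the practice-level variance is stable. At 0.5 it is only 0.09/(0.09 + 0.25) = 0.26. The highest rates in step 2 should therefore carry little weight. The number of oncologists may also be small: section 5.5 merges two groups for lack of providers, section 5.6 excludes others, and section 9 folds APPs into their oncologists.

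Some further inferences are tempting but not supported:

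- That the palliative care trial in lung cancer is a source of practice shocks in the main analysis. Section 5.6 excludes visits of patients enrolled in it; they return only in a sensitivity analysis.
- That peer comparison creates such shocks. Section 5.1 compares providers across the health system, so much of that effect is common to all practices and falls to the period effects.
- That the clinician-level analysis is pointless. It cannot reveal practice-level variation, but it does check how APPs are attributed to oncologists.

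Finally, the Poisson simulation is not the planned model. The binary simulation answers most of that, with similar results.

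**Conclusion.** The mismatch between the randomised unit and the clustering level is real and is written into the protocol. The primary standard error can be too small and the type I error can exceed 0.05; no planned analysis would show it.

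A reader might infer that the type I error certainly exceeds 0.05 because of the clustering level, or that a positive result would be an artefact. The documents do not support either, since both depend on a variance and a number of oncologists that they do not give. Under the assumptions of step 3, rejection is about 9-11% at SD 0.2 and 10-13% at SD 0.3. Of this, the excess over the 6-8% seen at SD zero is what shared practice shifts add. The direction is well established; the size in this trial is not known.

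**What to change.** - Keep the planned model, with practice and period effects, for the point estimate.
- Take the primary p-value and confidence interval from a permutation test that re-randomises practice start dates exactly as the trial did. Record the allocation procedure, including whether each date took one practice per stratum, so that the reference set (576, 2,520 or another number) is fixed before outcomes are analysed. Obtain the interval by inverting the test.
- Report a practice-clustered variance with a small-sample correction and a t reference as support only, noting that with eight clusters it may stay somewhat inflated. Do not replace oncologist clustering with plain practice clustering and a z test.
- Move oncologist clustering to a sensitivity analysis, and keep the clinician-level analysis as a check on APP attribution.

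The cost is revised analysis wording and a short program, with no new data. The interval will be wider, by an amount that depends on the unknown practice-by-period variation.
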